### Sample size justification and data analysis

This sample size calculation justifies our ability to assess the sensitivity and specificity of mD-SPA in its identification of the ACLR (i.e., case) and control groups. A total sample size of 250 (125 ACLR and 125 control) provides 88% power to detect a minimal change of 10% in sensitivity/specificity based on the exact binomial test. This sample size also has 80% power to detect an 8% improvement in prediction accuracy of mD-SPA relative to MC based on McNemar’s test. These calculations assume a minimal sensitivity and specificity of 90% for mD-SPA and that the proportion of discordant pairs of classification between the two measurement systems is 10%. The target significance level is assumed to be two-sided at 0.05 (PASS 2021 v*21*.*02*).

The continuous outcome times for DJ2, STS, and gait speed will be modeled using mixed effects models with person-specific random intercepts. These models will be weighted with the inverse of each person’s probability of belonging in their actual ACLR group, based on their separately modeled propensity for being in that group. The models will also adjust for the explanatory variables in the propensity score model, thereby enjoying the analytic property of being doubly robust. Statistical significance will be justified for multiplicity within the models of DJ2, STS, and gait speed using the standard Benjamini-Hochberg procedure to control for false discovery.

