A control cohort will be recruited through study finder (institutional study database), and study recruitment flyers will be distributed throughout the participating institutions. All attempts will be made to match the cases and control by sex, body mass index (BMI), and age.

Interested individuals from both groups will be asked to complete a REDCap eligibility screener and will be directed to a summary explaining the research and electronic consent if found eligible. If consent is given, contact information and basic demographic data will be obtained through REDCap. A study member will then contact eligible and consented individuals to schedule their data collection time.

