### Motion capture processing

MC data will be analyzed in two ways: 1) traditional MC data analysis will occur using variables extracted from averaged trial data, and 2) MC data will be subjected to the same machine learning algorithms outlined in the MDS processing section. The difference is that there are specific variables for MDS and MC. Extracted MC variables will include: internal rotation of the knee, pronation of the foot, the difference between inter-knee distance, forward displacement of the ACLR hip relative to the uninjured hip, sagittal and frontal hip and knee angular deficits at peak knee flexion angle, sagittal plane hip and knee displacement at peak knee extension angle, sagittal knee and hip displacements during weight acceptance, sagittal knee and hip displacement at midstance, and peak knee flexion and displacement. Data will be analyzed, and movement variables extracted from processed data using Visual 3D (C-Motion, Inc., Boyds, MD) and custom programs written in MatLab (The Mathworks, Inc., Natick, MA).

Traditional MC processing occurs by calculating inverse dynamics using Visual 3D and/or custom MatLab programs. Note that the selected tasks and variables represent measures that are expected to be identifiable using MDR, but not necessarily by MC. It is expected that MC will successfully measure the DJ2s, will be marginally successful at measuring STS, and will be unsuccessful at measuring gait speed on a level treadmill. The data will be processed using typical MC methods. MC data will be cleaned and preprocessed (including filling in missing data) using methods established for software programs Cortex 8 and Visual 3D. Data will be filtered using a 4th order, zero-lag low-pass Butterworth filter using MatLab filtfilt with a 10 Hz cutoff frequency.

The MC data will help us to effectively compare the accuracy of the MC system to that of MDR. Due to their heterogeneity, the two traditional sets of pre-processed data will not be statistically comparable. As such, we will use similar machine learning techniques to process the MC data, so that we are able to determine the accuracy and predictability of MC to correctly classify the ACLR group versus control. Accomplishing this will allow direct comparisons of discrimination, sensitivity and specificity for each of the techniques to successfully predict the control and ACLR groups.

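### Beyond best-effort matching, confounder control is stated only for the task-time models, so residual imbalance in sex, BMI or age could inflate the headline accuracy of MDR and MC

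*Protocol article*

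**What the plan says.** Confounding is addressed in two places in the protocol article.

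- **Design stage (Study design).** The article states that "All attempts will be made to match the cases and control by sex, body mass index (BMI), and age". No ratio, tolerance or balance check is given. Cases are found through health records and the surgical schedule. Controls come from an institutional study database and flyers. Both groups are restricted to ages 18 to 40.
- **Analysis stage (Sample size justification and data analysis).** Times for the drop jump, sit-to-stand and gait tasks go into mixed models with inverse-propensity weights. In addition, "The models will also adjust for the explanatory variables in the propensity score model, thereby enjoying the analytic property of being doubly robust". The variables in the propensity model are not named.

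The classification analysis is described separately. Motion capture processing promises "direct comparisons of discrimination, sensitivity and specificity for each of the techniques to successfully predict the control and ACLR groups". The sample size rests on these measures: "A total sample size of 250 (125 ACLR and 125 control) provides 88% power to detect a minimal change of 10% in sensitivity/specificity", and "This sample size also has 80% power to detect an 8% improvement in prediction accuracy of mD-SPA relative to MC". Neither description mentions weighting, adjustment, stratification or a covariate-only comparator.

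**The concern.** The main hypothesis, at the end of the Introduction, is that MDR will outperform MC in identifying the high-risk group. The accuracy measures answer it; the task times do not. Yet the stronger confounder control is attached to the task times. Planning doubly robust models suggests that the sponsor does not expect matching alone to be enough, and the same reasoning applies to the classifiers, which use the same 250 people.

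The classifiers are exposed for three reasons:

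- The section on limitations concedes that machine learning will not show why a person was classified as they were.
- MDR features are partly extracted by dimensionality reduction, so they are not restricted to variables chosen for their link to the knee.
- Treadmill speed is each participant's own preferred speed.

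Any group difference in sex, BMI or age that shapes the signal could therefore be used. Part of what is reported as detection of a high-risk movement pattern could then be detection of who was recruited. If the two systems carry body size or sex to different degrees, their difference could be affected too.

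**Working it through.** **1. The plan's own figures.** Inputs from the sample size section: 125 per group, two-sided 0.05, mD-SPA sensitivity and specificity of at least 90%, 10% discordant pairs.

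- Exact binomial test, n = 125. The null value is not stated. Taking 80% against 90% as an assumption gives power 0.881, against the stated 88%.
- McNemar's test, 8-point difference, 10% discordant, exact conditional form. With 125 pairs, power is 0.801, against the stated 80%.

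Both figures reproduce. Neither depends on confounder control, so this point does not challenge them.

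**2. Where each protection applies.**

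| Analysis | Matching (best effort) | Propensity weights | Covariate adjustment |
|---|---|---|---|
| Task times | yes | yes | yes |
| Sensitivity, specificity, discrimination; MDR against MC | yes | none stated | none stated |

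**3. Accuracy from imbalance alone.** The article gives no expected imbalance, so the inputs are assumptions: three independent normal covariates, each with residual standardised difference d, fully recovered by the classifier, and no ACL-reconstruction signal.

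D = d × √3; AUC = Φ(D/√2); accuracy at the best cut = Φ(D/2).

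| d | D | AUC | Accuracy |
|---|---|---|---|
| 0 | 0 | 0.50 | 50% |
| 0.2 | 0.346 | 0.597 | 57% |
| 0.3 | 0.520 | 0.643 | 60% |
| 0.5 | 0.866 | 0.730 | 67% |

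With one covariate only, d = 0.2 gives AUC 0.556 and accuracy 54%; d = 0.5 gives 0.638 and 60%.

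**4. Imbalance added to a real signal.** If the signal alone gives accuracy A and is independent of the covariates, its separation is S = 2Φ⁻¹(A). The combined accuracy is Φ(√(S² + 3d²)/2).

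| A | S² | d = 0.3 (3d² = 0.27) | d = 0.5 (3d² = 0.75) |
|---|---|---|---|
| 60% | 0.257 | 64% | 69% |
| 80% | 2.833 | 81% | 83% |
| 90% | 6.570 | 90.5% | 91% |

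The lift is up to about 9 points when the true signal is weak, and about 1 point or less at 90%. A weak signal is plausible, because cases must be medically cleared and anyone who limps is excluded.

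**5. What weighting would do.** Take one assumed imbalance: one sex makes up 60% of cases (75 of 125) and 40% of controls (50 of 125). A rule that calls that sex a case has sensitivity 75/125 = 0.60 and specificity 75/125 = 0.60. The propensity of being a case is 0.6 in that sex and 0.4 in the other. The weighted counts among cases are 75/0.6 = 125 and 50/0.4 = 125, so weighted sensitivity is 125/250 = 0.50. Among controls they are 50/0.4 = 125 and 75/0.6 = 125, so weighted specificity is 0.50. The spurious accuracy disappears. The effective number per group is 250²/(75/0.6² + 50/0.4²) = 62,500/520.8 = 120, against 125.

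**The case against.** **Matching already covers the classification analysis.** A reader might infer from the data analysis section that nothing protects the accuracy measures. That is wrong. Matching on sex, BMI and age defines the sample, so it protects every analysis, and the age limits add to it. What remains is that the matching is worded as an attempt and that no stated analysis deals with any shortfall.

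**A condensed article may leave this to the full protocol or SAP.** This has force. Nothing says that the accuracy measures will be left unadjusted. But the article does say where weighting and adjustment apply, and it names only the task-time models. A sponsor following it as written would not extend them to the accuracy analysis.

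**The imbalances are assumed.** This stands. No figure in the article supports 0.2 to 0.5, the upper end would be a failed match, and the calculation supposes that the signal fully reveals the covariates. The extracted MC variables are largely joint angles and relative displacements, which need not carry body size.

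**The device comparison is within person.** This stands in large part. Both systems record the same people simultaneously, so imbalance is common to both and bears on each system's own accuracy more directly than on the difference. A reader might infer that an MDR advantage would merely be better detection of body habitus. The article does not support that. It would require the two systems to use the covariates to different degrees, which is possible because their inputs differ, but nothing shows or sizes it.

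**Conclusion.** The point holds as a gap in the analysis stage. Matching is the only confounder control stated for the headline sensitivity, specificity and discrimination, while the task-time models also have weighting and adjustment. Residual imbalance could inflate each system's apparent accuracy. Under the assumed imbalances, covariates alone would give 57% to 67% accuracy (AUC 0.60 to 0.73).

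It would be too strong to infer that a reported accuracy near the planned level could be an artefact of imbalance. "These calculations assume a minimal sensitivity and specificity of 90% for mD-SPA", and imbalance of this size does not reach that on its own. The effect is zero if matching succeeds, small if the true signal is strong, and matters most if the signal is weak. Any effect on the MDR-MC difference is conditional on the devices using covariates differently. This is a worthwhile improvement to the plan; it does not invalidate the study.

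**What to change.** Pre-specify two additions to the accuracy analysis:

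1. Compute propensity-weighted (or covariate-adjusted) sensitivity, specificity and AUC for both MDR and MC, using the propensity model already planned for the task times. State that this model contains at least sex, BMI and age. Report these alongside the unweighted results.
2. Report the AUC of a classifier that uses age, sex and BMI alone, evaluated in the same way as the device classifiers, with each device's gain over it.

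Sex, BMI and age are already needed for matching, so no new data and no change to recruitment are required. The cost is a little more analysis and a small loss of precision from weighting. In the 60/40 example above, the effective number falls from 125 to 120 per group; a larger imbalance would cost more.

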## Discussion

### 1) Feasibility of using MDR

Here we propose a novel methodology using MDR to observe human movement and identify micro-movements indicative of high-risk for MSKI. MDR’s ability to identify subtle differences in movement patterns from the presence or absence of a foam wedge in a shoe’s heel has already been demonstrated in our previous study [12]. This reflects the potential of using MDR for detecting clinically relevant movements that are undetectable by the human eye. Individuals who have undergone ACLR are at high risk for additional surgeries following their initial reconstruction, making them a population at elevated risk. Successfully completion of this protocol will help us to identify this high-risk group with greater accuracy and predictability.

Moving forward, we see significant clinical utility for this technology. MDR technology is highly accurate and requires minimal training to operate. It is also compact, inexpensive, and portable, making it easy to place in a clinical setting or for use in the field. Future aims will determine if retrospective analysis can identify athletes that have incurred injury. Ultimately, we will use these data sets to better understand and refine how MDR identifies individuals at high risk. With this knowledge, we will have information to guide the prospective identification of high-risk individuals for MSKI. These factors may make MDR a potential assessment tool that can have large-scale applications in across a broad spectrum of clinical settings.

### 2) Superiority of MDR to MC

MC is limited by the measurement resolution of the system (typically 1.2–1.5 mm) which, as stated earlier, is on par with visual observation. We have previously shown that MDR can accurately identify subtle changes in movements patterns not detectable by the human eye [12]. Due to its potentially superior measurement sensitivity, MDR represents a viable method for identifying sub-visual risk markers in post-rehabilitation ACL reconstruction patients.

Based on previous work we hypothesize that MDR’s threshold for discriminating subtle movement patterns will be lower than that of MC for squat jumps [12], but the effectiveness in identifying movement pattern changes for other tasks is unknown. We will compare MC with MDR while participants perform drop jumps, sit to stand from a chair, and walk on a treadmill. We hypothesize that MDR will be superior to MC in differentiating these movements in an ACLR group compared with controls. Completion of this aim will provide evidence that MDR is noninferior and likely superior to the current gold standard. This will continue to support the tremendous clinical potential of this inexpensive and portable technology.

Successful completion of this study will provide a sound basis from which to conduct future large-scale prospective clinical trials to expand detection using MDR for specific MSKI injury patterns. This will in turn allow for predictive identification of those injury patterns prior to an actual MSKI. The ability to identify a high-risk MDS pattern is a novel approach that may provide primary prevention to those at high-risk of MSKI. We hypothesize this will in turn allow for targeted focus of limited resources for high-risk populations, in hopes of dramatically reducing patient morbidity, mortality, and associated healthcare costs.

## Methodological limitations and solutions

There are some limitations to using machine learning in the clinical setting. Machine learning will not explain why or how the movements indicate the level of participant risk. Machine learning algorithms create a “black box” phenomenon in which only the input and output data can be seen and not the details of how the processing occurred [7]. For instance, if a participant has significant valgus knee collapse as a risk factor for ACL injury, the algorithm might accurately classify them as high-risk without identifying knee valgus as the root cause of the increased risk. Fortunately, validated injury prevention programs exist [22–24], and the majority are exercise based. In general, the focus has been on improving the quality of athletes’ functional motion through plyometric, agility, and strength training [22–24]. However, universal implementation of such prevention programs is another limitation that the developed mD-SPA algorithm can help overcome [25]. The mD-SPA algorithm could potentially help direct limited preventative resources towards high-risk populations. Ultimately, continuing future data collection will enhance our algorithms by providing the training models with substantially more data to enable further enhancement of their accuracy and significance.

Another limitation is the complexity of MSKI, which is determined by many extrinsic and intrinsic risk factors [26]. Some of these risk factors are: history of injury, previous work restrictions, or lower perceived recovery from injury [9]. Inevitably there may be genetic factors that also play a role that would be of interest as well. Algorithms will need to be strengthened by adding data points taking into consideration the aforementioned risk factors.

A final limitation of MDS processing is its reliance on the impaired resolution of the short-term Fourier transform (STFT). As the duration of data collection increases, the STFT time resolution worsens even as frequency resolution improves. The opposite is also true. However, we were able to overcome this limitation as preliminary work showed that the STFT is sufficiently resolute to illustrate the overall structure of the MDS, even if it is not the optimal tool for subsequent feature extraction and classification.

## Conclusion

We describe the rationale and methodology of a case-control study using novel MDR to detect MSKI and identify individuals in a high-risk group. We expect this novel approach to be accurate and outperform the current gold standard of MC. Future translational studies will determine utility in the context of clinical primary care. Findings from this study may lead to larger prospective trials that will develop a database of micro-Doppler signatures that can identify movement patterns associated with MSKI.
